### Power analyses and sample size determination

2.3

The first aim of the study is to establish the relationship between local GABA and glutamate neurotransmitter concentrations, structural and functional network connectivity, and physiological measures of auditory/language network functioning. The estimated effect size for this aim is approximately 0.2223. This is estimated based on the literature showing a significant correlation between GABA+/Cre concentration and MEG evoked gamma power that range from 0.37-0.53 (49, 52, 56, 80). To our knowledge there is not any existing data on the correlation between the other predictor variables (DWI or functional MR connectivity) and MEG power and latency of evoked fields. However, given that both of these neuroimaging predictor variables have been shown to be aberrant in adolescents with ASD and reflect network-level structural and functional dysfunction, we predict a correlation between these neuroimaging measures and the proposed MEG measure of at least 0.15. Thus, in order to maintain 80% power with a type-I error rate of 5% and a type-II error rate of 20% we will enroll 86 ASD participants with a planned evaluable N=55 accounting for attrition.

The second aim of the study is to evaluate target engagement and the acute effects of active cTBS compared to sham cTBS on auditory/language network functioning. With planned evaluable N=55 and the minimal detectable effect (given Lehr’s equation (81)), the minimum detectible effect size is 0.38 standard deviation units, between a small (.2) and medium (.5) effect size in Cohen’s effect size taxonomy (82). We believe this is a reasonable effect size to expect given the literature. A recent study found an effect size of 0.7 on MRS GABA+/Cre concentration and 0.39 on MEG indices of sensory (visual) processing immediately following a single session of cTBS [95]. Therefore, we believe this aim is adequately powered.

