### Study design

2.1

This study employs a within-subject crossover design whereby participants receive both active and sham cTBS on different days based on a randomized blinded code that is entered into the TMS machine before each session. The crossover design was chosen because of the documented heterogeneity of neuroimaging outcomes within the ASD population as well as the interindividual variability in response to cTBS and other rTMS protocols. Therefore, it was determined that a between-subject design would be less powerful in determining the acute effect of cTBS on these neuroimaging outcomes.

Participants, study staff members and all other study personnel involved in TMS administration, data collection, or data analysis are blinded to whether sham or active stimulation is delivered during each cTBS session.

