##### MEG

2.4.2.1

MEG Data is acquired using a sampling rate of 1200Hz on a 275-channel MEG (CTF MEG NEURO INNOVATIONS, INC.) system. During acquisition, participants lay in the supine position on a comfortable bed with their head in the sensor helmet. Three fiducial marker coils are placed relative to anatomical landmarks: 1.5 cm superiorly to the nasion and 1.5 cm anteriorly to the left and right periauricular points along the line between the tragus and lateral canthus. These coils are activated at the beginning and end of the acquisition to localize the head within the MEG device and coarsely assess head movement during the scan. Directly prior to data acquisition, the localizer coils are registered to the anatomical MRI using Brainsight Neuronavigation software (Rogue Research, Canada). Both resting-state and task data are acquired. Prior to data acquisition hearing thresholds are determined by presenting 1000 Hz tones (300 ms duration, 10 ms rise time) to each ear sequentially and monotonically decreasing loudness until sensation level (SL) has been determined for each ear. Sounds for the MEG tasks are presented at approximately 45 decibels above SL. MEG recording sessions last ~45 minutes, and consist of the following paradigms:

An M100/M50 task, consisting of binaurally presented 500Hz tones, with a variable inter-trial interval (ITI) using the task reported in Roberts et al. (91). Note, there is a developmental trajectory in response to these stimuli with adults showing a prominent evoked field peak around 100 milliseconds, with an absent and/or less reliable peak at 50 milliseconds (92, 93) and the opposite (a more pronounced 50 millisecond peak) in children and especially those with ASD (94).Auditory 40 Hz steady-state task (ASSR), presenting 200 trials of 40 Hz amplitude modulated (AM) 500Hz sinusoidal tones (500 ms long, 45 dB SL) with a jittered 1.5 sec inter-stimulus interval as in Edgar et al. (63),.Resting MEG: 5 minutes eyes open in a completely dark room (with short periods of interspersed dim light) and 5 minutes eyes closed in a lighted room (with short periods of interspersed eyes open) as in Edgar et al. (95). Resting MEG was only collected in the eyes closed lighted room condition for the pilot phase.Oddball auditory task with interleaved/a/and/u/vowel stimuli as in Roberts et al. (96).

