### Statistical analysis

2.5

Multiple linear regressions will be conducted to evaluate whether baseline MRS measures of local GABA and glutamate concentration, structural topography/connectivity, and/or functional activity/connectivity explain a significant proportion of the variability in MEG measures of auditory/language processing. These analyses will quantify the relationship between these measures and to what extent they may contribute to a fusion biomarker model for language processing deficits in ASD (e.g., (139)). To evaluate the effect of a single session of cTBS on MRS, fMRI, and MEG outcome measures, Factorial ANCOVAs will be conducted with time-point (pre-post) and condition (active, sham) as within-subjects variables. Other anticipated covariates in these analyses include age, gender, baseline symptom severity, and medication use. In addition to the targeted region (left pSTC), we will repeat the planned fMRI BOLD and connectivity analyses using right pSTC, left and right IFG, and a non-connected (control) cortical visual network with a temporal and frontal node to explore the spread of the effect of the cTBS from the targeted region to other structurally and functionally connected regions compared to a control network. Pearson correlation coefficients will be used for the exploratory analyses, to characterize the relationship between the neuroimaging and electrophysiological indices and baseline behavioral symptom presentation including assessments of general functioning, autism symptom severity, and auditory and language processing. As there may be intrasubject variability in these measures (independent of the cTBS intervention), we will evaluate the reliability of the baseline/pre-stimulation MEG, MRS, and fMRI outcomes by calculating the interclass correlation coefficient (Model: 2-way mixed effects, Type: mean of k measurements and Definition: absolute agreement) as a measure of test-retest reliability.

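### Aim 2's detectable effect of 0.38 has no stated SD unit, so adequate power for MEG is not established, and the planned interaction uses the pre-stimulation values inefficiently

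*Protocol article*

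**What the plan says.** Section 2.1 of the protocol article sets the design: "This study employs a within-subject crossover design whereby participants receive both active and sham cTBS on different days". Section 2.3 gives the Aim 2 power statement. It begins "With planned evaluable N=55 and the minimal detectable effect (given Lehr’s equation (81" and arrives at this: "the minimum detectible effect size is 0.38 standard deviation units, between a small (.2) and medium (.5) effect size". The benchmark follows: "A recent study found an effect size of 0.7 on MRS GABA+/Cre concentration and 0.39 on MEG indices of sensory (visual) processing". The section then concludes that the aim has adequate power.

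Section 2.5 gives the analysis: "Factorial ANCOVAs will be conducted with time-point (pre-post) and condition (active, sham) as within-subjects variables". The further covariates it anticipates are age, gender, baseline symptom severity and medication use. None of these is the imaging value taken just before stimulation in the same session; that value enters as one level of the time factor.

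No within-participant correlation and no SD of change is given. Section 2.5 says that test-retest reliability will be evaluated from the study's own data.

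**The concern.** An effect in SD units means nothing until the SD is named. Three candidates are available here: the SD of a single measurement, of a pre-post change, and of the active-minus-sham difference in change. Section 2.3 names none of them. It still places 0.38 between Cohen's small and medium benchmarks and sets it beside two published effects whose SD is also not stated. The comparison supports the adequacy conclusion only if all these figures share one unit.

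This matters most for the MEG outcomes, because the published MEG effect exceeds the stated limit by only 0.01.

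There is also an efficiency question. An interaction with pre and post as factor levels amounts to subtracting each pre value in full. When the pre difference predicts the post difference imperfectly, full subtraction adds noise that covariate adjustment would remove.

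**Working it through.** **Inputs.** Evaluable N = 55, the stated limit of 0.38, and published effects of 0.7 and 0.39 (all section 2.3). Two-sided 5% and 80% power: section 2.3 states 5% and 80% for Aim 1, and Lehr's rule implies the same for Aim 2. The same-session pre-post correlation ρ is not in the document and is treated as an assumption.

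**Step 1: reproduce 0.38.**
- Lehr's rule, paired or one-sample form: √(8/55) = 0.381.
- Normal approximation: (1.960 + 0.842)/√55 = 0.378.
- Exact paired t-test: 0.385; power at 0.38 is 79.0%.
- Two-group form with 55 per group: √(16/55) = 0.539, which does not match.

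So 0.38 is in SDs of a within-participant contrast.

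**Step 2: identify the contrast.** In a two-by-two within-participant design, the test of active against sham on change is a one-sample test of

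D = (post − pre, active) − (post − pre, sham).

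For that test 0.38 is right, in SDs of D.

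**Step 3: convert to outcome SDs.** Let σ be the SD of one measurement. With equal variances and one common correlation for all between-session pairs, SD(D) = 2σ√(1−ρ). The limit in outcome SDs is therefore 0.385 × 2√(1−ρ). At ρ = 0.5, for example, 0.385 × 2 × 0.707 = 0.54. The last column gives power if the published MEG effect of 0.39 is in outcome SDs.

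| ρ (assumed) | Limit, outcome SDs | Power for 0.39 |
|---|---|---|
| 0.4 | 0.60 | 45% |
| 0.5 | 0.54 | 52% |
| 0.6 | 0.49 | 61% |
| 0.7 | 0.42 | 74% |
| 0.75 | 0.385 | 81% |
| 0.8 | 0.34 | 89% |
| 0.9 | 0.24 | 99% |

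The limit is above 0.38 when ρ is below about 0.75 and under it when ρ is higher.

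If instead 0.39 is in SDs of D, power is about 81% whatever ρ is. For the GABA effect of 0.7 in outcome SDs, power is about 86% at ρ = 0.3 and 95% or more from ρ = 0.5 upward.

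**Step 4: efficiency of the planned contrast.** Let P be a participant's active-minus-sham difference in pre values, Q the same in post values, and r their correlation. With equal variances v:
- Interaction: Var(Q − P) = 2v(1−r).
- Q adjusted for P: v(1−r²).
- Ratio: (1−r²)/[2(1−r)] = (1+r)/2.

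The variance is 50% lower at r = 0, 25% lower at r = 0.5 and 20% lower at r = 0.6. Simulation gave ratios of 0.51, 0.71 and 0.81 at r = 0, 0.4 and 0.6, against 0.50, 0.70 and 0.80 from the formula.

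If every between-session correlation equals ρb, then r = (ρ − ρb)/(1 − ρb). Two examples:
- ρ = ρb = 0.5 gives r = 0, and the limit falls from 0.54 to 0.54 × √0.5 = 0.385 outcome SDs.
- ρ = 0.7 and ρb = 0.5 give r = 0.4, and the limit falls from 0.42 to 0.42 × √0.7 = 0.35.

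Pre values precede stimulation and the order of active and sham is randomised. Absent carry-over, P has mean zero and both analyses estimate the same effect.

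**The case against.** The strongest reply is that nothing has been miscalculated, and that is right. A reader might infer an arithmetic error, or a clash between a paired limit and a difference of differences. There is none, because 0.38 is the proper limit for the interaction on the scale of its own contrast.

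A reader might also infer that the true limit is usually larger than 0.38, or that 55 participants are too few. The documents do not support either. Both depend on ρ, which is not given, and above about 0.75 the outcome-SD limit is smaller than 0.38. Pre and post scans sit immediately either side of a 40-second stimulation, so a high ρ cannot be ruled out.

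Nor does the text say that its unit is the ordinary outcome SD. Cohen's labels are also applied to paired effects. If 0.39 was standardised by the same contrast, the comparison is coherent and power just reaches 80%.

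On the analysis, the factorial model is a valid test and the proposed replacement is a gain in precision. The gain is largest when within-session and between-session correlations are equal, and it shrinks as r rises.

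All of this stands, and it limits the point. It does not supply the missing unit, on which the adequacy statement for MEG rests.

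**Conclusion.** The point holds as an undefined unit and an avoidable loss of efficiency. The figure of 0.38 is correct in SDs of the within-participant double difference, but section 2.3 does not say so and compares it with benchmarks of unstated unit. Adequate power for the MEG outcomes is therefore not established. It is about 81% at best on the contrast scale, with essentially no margin, and between 45% and 89% for ρ from 0.4 to 0.8 if the benchmark is in outcome SDs. The conclusion for GABA is much less sensitive.

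The conversions assume equal variances and equal between-session correlations; the efficiency ratio assumes equal variances of the pre and post differences. A full analysis plan, not shown here, may refine the model, but the figure, the comparison and the conclusion stand in the article itself. This is worth changing but is not a flaw that invalidates the plan.

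**What to change.** 1. **Section 2.5.** For Aim 2, estimate the active-minus-sham difference in post values, adjusted for the active-minus-sham difference in same-session pre values, in place of the time-by-condition interaction. This is one regression per outcome on values already collected. It costs one degree of freedom and needs no extra participants or visits.

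2. **Section 2.3.** State that 0.38 (exact 0.385) is in SDs of the within-participant contrast. Add the outcome-SD equivalents for ρ from 0.4 to 0.9, say which SD the published 0.7 and 0.39 use, and limit the adequacy statement for MEG accordingly. The cost is wording, and a stated limit that may look less favourable.

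3. **Editorial.** Check the source of the benchmark: "0.39 on MEG indices of sensory (visual) processing immediately following a single session of cTBS [95". The square bracket departs from the article's usual citation style. In section 2.4.2.1 the same number is attached to the resting-recording method ("Resting MEG: 5 minutes eyes open in a completely dark room"), so the SD behind the benchmark cannot be traced at present.

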### Procedures

2.4

#### Medical, neuropsychological, and neurodevelopmental assessments

2.4.1

After completing informed consent, all participants (across both phases of the study) receive a thorough medical history and brief neurological and physical exam by a licensed physician or nurse practitioner, where concomitant medications are also reviewed. Participants then complete several standardized neuropsychological and neurodevelopmental assessments and rating scales. The Social Responsiveness Scale (SRS-2) and Wechsler Abbreviated Scale of Intelligence (WASI-II) were completed in the pilot and main phases, and the remaining measures listed below will be administered only to participants in the main phase of the study (ASD).

##### The social responsiveness scale, second edition

2.4.1.1

The SRS-2 is a 65-item scale completed by the Healthy Volunteer or the parent/caregiver on behalf of their child and is designed to screen children and adults for autistic traits (83). There is a self-report and a parent/caregiver-report form, in which the individual completing the form rates each item based on a 4-point Likert scale from ‘not true’ to ‘almost always true’ regarding their (for the Healthy Volunteers)/their child’s (for the parent/caregiver of the ASD participant) behavior in the previous six months. Items within each of the two subscales and a composite score are calculated into a standard raw score and T-score.

##### The child behavior check list

2.4.1.2

The CBCL is a 118-item scale completed by the parent/caregiver on behalf of their child and is designed as a standardized assessment of children’s symptomatology across several domains including anxiety, attention problems/hyperactivity, conduct problems, depression, oppositional defiant, social problems/immaturity, and somatization (84). The individual completing the form rates each item based on a 3-point Likert scale (“Not True”, Somewhat or Sometimes True” and “Very True or Often True”) regarding their child’s behavior in the previous six months. A total score and subscale scores (corresponding to specific symptom/DSM diagnostic domains) are calculated.

##### Wechsler abbreviated scale of intelligence, second edition

2.4.1.3

The WASI-II is a brief, reliable measure of general cognitive ability as well as a verbal comprehension and perceptual reasoning index score (85). It is appropriate for use in children and adults ages 6-90. Healthy Volunteers and Adolescents with ASD will be included if their FSIQ>70, thus excluding participants with intellectual disability.

##### Vineland adaptive behavior scales-3^nd^ edition

2.4.1.4

The VABS-3 is a semi-structured parent/caregiver interview designed to evaluate adaptive functioning of their child in four domains: Communication, Daily Living Skills, Socialization, and Motor Skills (86). Standard scores are provided for each domain (with the exception of Motor Skills for children over age 9) and for an overall Adaptive Behavior Composite Score.

##### The autism diagnostic interview-revised

2.4.1.5

The ADI-R is a structured interview conducted with the parents/caregivers of individuals with ASD (87). It covers their child’s full developmental history and generally takes one to two hours. Parents/Caregivers are asked 93 questions about either their child’s current behavior or behavior at a certain point in time. The interview is divided into four main sections assessing the quality of social interaction, language and communication, restricted and repetitive behaviors, and maladaptive behaviors such as self-injury, aggression, and over activity. The interview determines a rating score for each question, and a total score is calculated for each of the content areas. For the purposes of this study, ADI scores are used as a baseline measure for exploratory analyses. Eligible participants for the main phase of the study have received an ASD community diagnosis per DSM-IV or DSM-V criteria.

##### Expressive vocabulary test, third edition

2.4.1.6

The EVT-3 is an individually administered, norm-referenced instrument that assesses expressive vocabulary and word retrieval for children and adults (88). The test contains training items and 190 test items arranged in increasing difficulty. For each item, the examiner presents a picture and reads a stimulus question, and the examinee responds with one word that provides an acceptable label, answers a specific question, or provides a synonym for a word that fits the picture.

##### Peabody picture vocabulary test, fifth edition

2.4.1.7

The PPVT-5 is a norm-referenced instrument for measuring receptive (hearing) language processing (89). It is appropriate for use in children and adults as young as 2.5 years old. The test contains training items and 228 test items, each consisting of four full-color pictures as response options on a page. For each item, the examiner says a word, and the examinee responds by selecting the picture that best illustrates that word’s meaning.

##### Clinical evaluation of language fundamentals

2.4.1.8

The CELF-5 is a standardized assessment of language used to diagnose language disorders in individuals 5 to 21 years of age (90).

#### Imaging acquisition procedures

2.4.2

##### MEG

2.4.2.1

MEG Data is acquired using a sampling rate of 1200Hz on a 275-channel MEG (CTF MEG NEURO INNOVATIONS, INC.) system. During acquisition, participants lay in the supine position on a comfortable bed with their head in the sensor helmet. Three fiducial marker coils are placed relative to anatomical landmarks: 1.5 cm superiorly to the nasion and 1.5 cm anteriorly to the left and right periauricular points along the line between the tragus and lateral canthus. These coils are activated at the beginning and end of the acquisition to localize the head within the MEG device and coarsely assess head movement during the scan. Directly prior to data acquisition, the localizer coils are registered to the anatomical MRI using Brainsight Neuronavigation software (Rogue Research, Canada). Both resting-state and task data are acquired. Prior to data acquisition hearing thresholds are determined by presenting 1000 Hz tones (300 ms duration, 10 ms rise time) to each ear sequentially and monotonically decreasing loudness until sensation level (SL) has been determined for each ear. Sounds for the MEG tasks are presented at approximately 45 decibels above SL. MEG recording sessions last ~45 minutes, and consist of the following paradigms:

An M100/M50 task, consisting of binaurally presented 500Hz tones, with a variable inter-trial interval (ITI) using the task reported in Roberts et al. (91). Note, there is a developmental trajectory in response to these stimuli with adults showing a prominent evoked field peak around 100 milliseconds, with an absent and/or less reliable peak at 50 milliseconds (92, 93) and the opposite (a more pronounced 50 millisecond peak) in children and especially those with ASD (94).Auditory 40 Hz steady-state task (ASSR), presenting 200 trials of 40 Hz amplitude modulated (AM) 500Hz sinusoidal tones (500 ms long, 45 dB SL) with a jittered 1.5 sec inter-stimulus interval as in Edgar et al. (63),.Resting MEG: 5 minutes eyes open in a completely dark room (with short periods of interspersed dim light) and 5 minutes eyes closed in a lighted room (with short periods of interspersed eyes open) as in Edgar et al. (95). Resting MEG was only collected in the eyes closed lighted room condition for the pilot phase.Oddball auditory task with interleaved/a/and/u/vowel stimuli as in Roberts et al. (96).

##### Structural MRI

2.4.2.2

All MRI and MRS data are acquired on a General Electric (GE) MR-750 3T scanner using a 32-channel head coil. For targeting of the TMS and registration of the fMRI, DWI, and MRS scans, the following structural MRI sequences are acquired (1): A 6-minute high-resolution T1 weighted Magnetization Prepared Rapid Gradient Recalled Echo (MP-RAGE) with repetition time (TR) = 7.7 ms, echo time (TE) = Min Full, flip angle = 7 degrees, a spatial resolution of 1.0 × 1.0 × 1.0 mm^3^, and 176 slices; (2) A 1.5-minute T1 weighted Spoiled Gradient Recalled Echo (SPGR) with TR = 200 ms, TE = In phase, flip angle = 80 degrees, a spatial resolution of 0.8 × 0.9 × 3.0 mm^3^, and 20 slices; (3) A 2.5-minute fat suppressed T2 weighted with TR = 6553 ms, TE = 100 ms, flip angle = 125 degrees, a spatial resolution of 0.9 × 1.2 × 1.7 mm^3^, and 100 slices; (4) For electrical-field (EF) modeling, a 5.5-minute (nonfat-suppressed) T2 weighted with TR = 2500 ms, TE = Maximum, a spatial resolution of 1.0 × 1.0 × 1.0 mm^3^ and 176 slices. Electric field (e-field) modeling has been added to the main phase to optimize placement of the TMS coil.

